
## Methods

### Study Design and Setting

This cohort study is implemented in a single center and applies a pre-post mixed methods (qualitative-quantitative convergent) design. Participants are recruited from Prevention and Early Intervention Program for Psychosis (PEPP)–Montreal, the Douglas Mental Health University Institute in Montreal, Quebec. This program provides a comprehensive range of services for young people diagnosed with FEP and follows best practice guidelines for real-world settings [7,8]. Treatment includes psychiatric evaluation and follow-up, modified assertive case management tailored to meet the needs of young patients in the early phase of illness [8] including support toward treatment goals (eg, illness education, return to work or school, and crisis intervention), family support and intervention, and psychosocial group interventions (eg, physical, recreational, recovery, and support).

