Participants received detailed information concerning their participation including date, time, and duration of scheduled meetings, interviews, and activities related to study participation. In addition, they were contacted 24 hours prior to any scheduled interviews to confirm their participation. They were contacted according to their preferences either by phone, e-mail, or in person when attending the clinic. After providing written informed consent, the research assistant administered the baseline measures, the results of which were also used to confirm clinical stability and eligibility to participate. In a subsequent HoryzonsCa Orientation Meeting, participants were oriented to the HoryzonsCa website and provided with login information. Participants were then able to access the website, at their convenience, over a period of 8 weeks. They were encouraged to log into the website at least 1 time per week for a minimum of 15 minutes per visit. Access to HoryzonsCa was in addition to the services that participants already receive from PEPP-Montreal. The Horyzons safety protocol [27] was adapted for this study and included an assessment procedure for risk of suicide attempt. This assessment has been implemented by members of the team in the context of other psychosocial intervention research projects with the same clinical population. All research team members were trained in the safety protocol. Given that it was the first time the website and safety protocol was used in a Canadian context, the results of this study will help identify potential modifications to improve the safety protocol for future research on HoryzonsCa. The details of the adapted safety protocol and withdrawal criteria are provided in Multimedia Appendix 1.

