#### Acceptability

*Acceptability* (TAM components of perceived ease of use and perceived usefulness) was measured through the HC-AUSI-Q and website use analytics. The HC-AUSI-Q is an adaptation of questionnaires used in the HoryzonsCa phase 1 adaptation study [30,31], the Horyzons Usability Questionnaire from the original Horyzons pilot study [27], and the Website Analysis and Measurement Inventory [47]. The interviewer-administered HC-AUSI-Q consists of a questionnaire and a semistructured interview that includes 16 close-ended and 10 open-ended questions on perceived ease of use, perceived usefulness, enjoyment, and safety. The questions pertaining to acceptability address the topics of general experience (eg, “I had a positive experience on Horyzons-Canada”), usefulness (eg, “Horyzons was useful to identify my warning signs for relapse”), and ease of use (eg, “Overall, the platform is easy to use”). Acceptability in terms of adoption was assessed using website use analytics (eg, frequency of log-ins and patterns of use over 8 weeks).

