### Analysis Plan

Following the convergent mixed methods model, the quantitative and qualitative data will first be analyzed separately and then considered for an integrated analysis of the findings [58]. The quantitative data (including website use data) will first be assessed using descriptive statistics (eg, frequencies). Specifically, to evaluate the acceptability and safety of HoryzonsCa, we will analyze quantitative feedback from the HC-AUSI-Q and website use by calculating proportions (ie, percentage of participants who indicate agree or strongly agree for specific items related to acceptability and safety; percentage of participants with at least 4 log-ins over the 8 weeks follow-up). To assess the potential efficacy of HoryzonsCa, paired samples *t* tests will be conducted on social functioning and clinical measures, and within-group effect sizes (Cohen *d*) will be reported for statistically significant changes between baseline and the 8 weeks follow-up. We will make Bonferroni corrections to reduce the inflation of alpha for multiple comparisons and determine a minimal clinically important difference to detect important changes over time. In addition, exploratory analysis of potential meditators and moderators of treatment effects will be conducted; for example, we will analyze the associations between website use and treatment effects to estimate the moderating role of website use. We will conduct the checks of assumptions prior to conducting analysis, including normality of the data, and will transform the data if needed. Two members of the research team (eg, a postdoctoral fellow and a research assistant) will review data quality (eg, missing data) and determine the best approach (eg, multiple imputation) to handle the missing data in consultation with a statistician and senior members of the research team. Quantitative data analysis will be supported using SPSS (IBM Corp; or R [R Foundation for Statistical Computing]).

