### Strengths and Limitations

There are several strengths to this research. First, in terms of preparing the intervention, we made adaptations to Horyzons to optimize its transferability from Australia to Canada, using a systematic approach and an eHealth adaptation framework, prior to its implementation [30,31]. The mixed methods design in this study is expected to provide an in-depth understanding of user experience and perspectives of HoryzonsCa. This mixed methods approach allows researchers to obtain a comprehensive view about the user experience and evaluate the potential impact of implementing such digital health innovations in Canadian health care settings.

Limitations of this study include a small sample size (N=20) and a single group, pre-post design. Due to this small sample size and a lack of a control group, we may not be able to detect treatment effects and impact of the intervention. Additionally, due to the short duration of follow-up (ie, 8 weeks), our findings regarding the acceptability, safety, and potential efficacy of HoryzonsCa will need to be interpreted with caution. Furthermore, our approach to exclude participants that score as moderately severe to extremely severe on suicidality (ie, due to recent suicidal ideations and behaviors, to mitigate the need for urgent intervention on a platform that is not monitored 24/7, and to reduce potential overexposure to comments that may be disruptive or distressing for other participants in the intervention) is not necessarily supported by predictive research and could even potentially exclude participants who may benefit from such an intervention [63,64]. Future research on HoryzonsCa should consider how such an online intervention platform can facilitate a recovery-oriented approach for all participants despite their score on a suicidality assessment while at the same time optimizing the safety of the online group environment. In addition, although the field of digital mental health is rapidly growing [23,61], we acknowledge that the limited evidence on the implementation of digital mental health interventions for people diagnosed with severe mental health disorders such as psychosis in Canada may limit the scope of our interpretations regarding the results. Nonetheless, the findings will help inform decision-making for scaling up the evaluation on HoryzonsCa to a larger implementation study.

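### Website use cannot be analysed as a moderator (or mediator) of treatment effects in a single-group pre-post study; the planned analysis can only describe an association between use and change

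*Protocol article*

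**What the plan says.** The Analysis Plan states that "exploratory analysis of potential meditators and moderators of treatment effects will be conducted" (the third-to-last word group evidently means mediators as well as moderators). It illustrates this with website use: "we will analyze the associations between website use and treatment effects to estimate the moderating role of website use".

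Four other parts of the protocol article bear on whether that is possible:

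- **Design.** Study Design and Setting: "This cohort study is implemented in a single center and applies a pre-post mixed methods (qualitative-quantitative convergent) design". Strengths and Limitations: "Limitations of this study include a small sample size (N=20) and a single group, pre-post design". The only effect quantity in the Analysis Plan is within-group change from baseline to 8 weeks (paired t tests, Cohen d).
- **When use is measured.** Outcome Measures, Acceptability: "Acceptability in terms of adoption was assessed using website use analytics (eg, frequency of log-ins and patterns of use over 8 weeks"). It is therefore a post-baseline variable.
- **Who determines use.** The recruitment and orientation section: "Participants were then able to access the website, at their convenience, over a period of 8 weeks". The description of the Horyzons platform adds that clinician moderators send weekly suggestions fitted to each person's needs, with a text notification, and that peer moderators contact users who have not logged in after a week.
- **Role of use as an outcome.** Objectives and Hypotheses makes log-ins an acceptability criterion: 60% of participants with at least 4 log-ins over 8 weeks.

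**The concern.** A moderator is a variable, not itself affected by treatment, across whose levels the treatment effect differs. A mediator lies on the path from a treatment contrast to the outcome. Both need a treatment contrast, and this study has none. Website use also fails the first definition for a second reason: it is behaviour during the intervention and a result of being offered it.

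What is at stake is how a correlation may be read. Someone who is recovering may log in more, and someone who is deteriorating may log in less. A motivated participant may both use the platform and improve through the specialized services that everyone continued to receive. If such a pattern is labelled a moderating role, it can be taken as evidence that more use gives more benefit. The pilot is meant to inform a larger study, so the label matters even in a subsidiary analysis.

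**Working it through.** The protocol article gives no model, effect size or power for this analysis, so there is no stated figure to reproduce. The check has three parts.

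**1. Identification.** For participant i, write the observed change as C = N + T. N is the change that would have occurred without the platform and T is that person's effect of the platform. Let U be website use. Then

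Cov(U, C) = Cov(U, N) + Cov(U, T).

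A moderating role of use would concern Cov(U, T). The study observes only the sum. In a controlled trial with a baseline variable in place of U, the comparator arm would supply the first term. Here there is no such arm, and even if there were, U would not exist in it because nobody there has access. The two terms cannot be separated at any sample size.

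**2. Can an association appear with no effect?** Set T = 0 for everyone. Let an unmeasured recovery or engagement trait load equally, with loading a, on use and on natural change, both with unit variance. The true correlation is then a². The table shows 20,000 simulated single-group studies of n = 20 per row, tested at two-sided 0.05. The loadings and the test level are assumptions, since the documents give neither.

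| Loading a | a² | Mean r | Studies with P<.05 |
|---|---|---|---|
| 0 | 0 | 0.00 | 5.0% |
| 0.3 | 0.09 | 0.09 | 6.4% |
| 0.5 | 0.25 | 0.25 | 18.6% |
| 0.7 | 0.49 | 0.48 | 62.0% |
| 0.8 | 0.64 | 0.63 | 89.8% |

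A use-change correlation therefore arises with nothing to moderate. The correlation centres on a², which does not depend on n, so a larger study would estimate the wrong quantity more precisely. Nothing in the documents says which loading applies. The table shows a range and is not a forecast.

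**3. Precision (secondary).** Inputs: n = 20 analysed (Results section, none lost at 8 weeks), an unadjusted Pearson correlation, and two-sided 0.05 before any Bonferroni correction. The last two are assumptions.

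- Critical |r| = t/√(t² + n − 2) = 2.101/√(2.101² + 18) = 0.444.
- 95% CI for r = 0.40 by Fisher z: atanh(0.40) = 0.424; half-width 1.96/√17 = 0.475; limits tanh(−0.052) and tanh(0.899), that is −0.05 to 0.72.
- Power at a true r of 0.3: Φ(atanh(0.3)·√17 − 1.96) = Φ(1.276 − 1.96) = Φ(−0.684), about 25%.
- True r needed for 80% power: tanh((1.960 + 0.842)/√17), about 0.59.

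**The case against.** The strongest reply is that the protocol already hedges. The analysis is called exploratory, and what will actually be done is to examine associations. Strengths and Limitations concedes that, with so few participants and no comparator, effects of the platform may go undetected. The sample-size section says efficacy testing is not the main objective. No hypothesis or success threshold depends on this analysis, and what the article expressly sends forward to the next trial is pre-post effect sizes for power and sample size, not a use-change association. All of that stands, and it sets the severity. It does not remove the point. Calling an analysis exploratory limits the strength of its evidence but does not make an unidentified quantity estimable. The stated limitation treats the missing control group as a problem of detecting effects and does not mention that use is post-baseline and self-selected.

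Several stronger readings are tempting, and the documents do not support them:

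- A reader might infer that the authors will present engagement as efficacy, or carry a dose claim into the next trial. Nothing in the article says so; the wording permits that reading but does not commit to it.
- A reader might call the absence of baseline adjustment an error. The article states no model for this association, and covariates are commonly left to a fuller document.
- A reader might treat the low power as the defect, or say that any significant coefficient must be overestimated. The precision figures describe N=20 and not identification. Overestimation is guaranteed only if the true |r| is below about 0.44.
- A reader might conclude that all such exploratory work should be dropped. Website use is given only as an example, and baseline characteristics can legitimately be studied as predictors of change.

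**Conclusion.** The point holds in this limited form. The plan names an estimand, the moderating role of website use on treatment effects, that a single-group pre-post design cannot identify, and the same applies to mediation. This conclusion rests on the stated design and on the timing, self-selection and outcome status of website use. It does not rest on the simulated loadings or on any assumption about the test.

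Its size is a matter of interpretation: what may be concluded from one exploratory analysis. No figure in the protocol is wrong on this point, and the primary acceptability conclusion is unaffected. Low severity, but worth correcting before results are reported.

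**What to change.** In the Analysis Plan, replace the mediator and moderator wording with text such as: *We will describe the association between website use and the 8-week score adjusted for baseline (or the pre-post change), with a 95% CI, as an exploratory analysis. Because there is no comparator and use is self-selected after baseline, no moderation, mediation or dose-response inference will be drawn.* Exploratory associations of baseline characteristics with change may stay if they are described as predictors of change and not as moderators of a treatment effect.

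The cost is two or three sentences, with the same data and no added analysis. What is given up is a label that the design cannot support. The article reports that data collection is complete and analysis is under way, so the same wording should govern the results report, with the change of description noted there.

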## Results

This study was funded by the Brain and Behavior Research Foundation (United States), Quebec Health Research Funding Agency (Canada), and the Canada Research Chairs Program (Canada), and was approved by the Research Ethics Board of the Centre intégré universitaire de santé et de services sociaux de l'Ouest-de-l'Île-de-Montréal on April 11, 2018 (#IUSMD 17-54). The study was registered as a clinical trial at [60] (ISRCTN43182105). Recruitment was initiated on May 10, 2018, and data collection occurred between August 16, 2018, to April 29, 2019. A total of 48 individuals were approached for the study, from which 20 were excluded (17 declined to participate, 1 was not reachable, 1 did not meet inclusion criteria, and 1 met exclusion criteria). The 28 remaining individuals provided informed consent and were invited to complete a baseline assessment, from which 4 did not attend for various reasons (eg, no longer interested, no longer attending clinic, or not feeling well). Among the 24 participants that completed the baseline assessment, 3 dropped out of the study before being given access to the intervention, and 1 was excluded from the intervention soon after team discussion of the baseline assessment due to not meeting inclusion criteria (ie, clinical stability). Upon completion of the baseline assessment and confirmation of eligibility criteria, a final sample of 20 participants were given access to the intervention and none of these were lost at 8 weeks follow-up. Participants were recruited over a 9-month duration (which was 3 times longer than our originally anticipated 3-month timeline), with a recruitment rate of approximately 3 participants per month. A total of 9 participants attended the focus group meetings of approximately 120 minutes each session (4 attended more than once). No adverse events related to the intervention occurred during the live pilot implementation. Further details on the results are expected to be submitted for publication in 2021.

## Discussion

### Importance of This Study

Psychotic disorders can have a profound impact on the individual, their caregivers, and society with regard to a loss of quality of life and productivity. Despite advances in early intervention, there remain ongoing challenges in treating this population, including preventing relapse and service disengagement, and sustaining improvements in symptoms and functioning over the long term. As such, accessible, sustainable, and engaging psychosocial services are needed to optimize care and outcomes for this population. The COVID-19 pandemic and public health guidelines for social distancing have compounded the urgent need for new models of service delivery to provide specialized services to patients with FEP. This study addresses this gap in health service research through leveraging HoryzonsCa, an online intervention with the potential to support recovery and prevent relapse in patients with FEP, during and post COVID-19.

In this paper, we have described the study protocol for pilot-testing HoryzonsCa, and it is the first study to implement and evaluate a live version of this online intervention in a Canadian context. This study is distinguished from previous research on Horyzons, as it is the first to be based on a systematic adaptation process [30,31] that considers geographical, cultural, and health care contexts. There is evidence to suggest that embarking on an adaptation process of an eHealth intervention (eg, considering language, culture, and context) can contribute positively to its adoption and effectiveness [31].

The Canadian context is distinguished from the Australian context in several ways that highlight the importance of Canadian-specific adaptation and testing of Horyzons. For example, there are differences in terms of history of colonization, such that Australia has a history of British colonization and Canada has both a British and French history, rendering certain health care settings particularly in Montreal to provide care in a bilingual context. This has implications for the adaptability of all features of the website intervention in terms of translation. There are also differences in the use of English terms and colloquialisms [31], and systems-level differences in community resources and how mental health services are organized and delivered. Indeed, based on our phase 1 research, we adapted several aspects of the intervention in relation to these differences, detailed in our previous publication, including but not exclusive to terms and colloquialisms, safety and moderation protocols, need help resources, terms of use, list of trigger words that will automatically be flagged by the system as indicating risk, and change to content and resources pertaining to employment/studying/volunteering to be in alignment with Canadian norms [30].

Furthermore, in comparison to Australia, the Canadian context lags in terms of implementation of digital health innovations [61]. Moreover, peer support legislation, policy, training, and provision is uneven across Canada [62]. These factors influenced our implementation of the intervention, particularly in relation to the hiring and training of the moderation team. For example, in previous Australian research on Horyzons, the clinician moderators were already working at the recruitment site delivering face-to-face services, with part of their time allocated to providing online moderation for Horyzons, whereas in the current context, the clinicians were ambivalent about making online moderation as part of their role, which may be due to the lack of experience and training in the delivering of online interventions [30]. As such, for this pilot study we decided to recruit a moderator external to the setting. Additionally, we had a limited pool of trained and experienced peer support worker workforce to recruit from and had turnover of 2 peer support workers (for reasons unrelated to the intervention) before being able to recruit a peer support worker that completed the duration of the project. However, it is noteworthy that this worker had limited experience in the delivery of online interventions and no employed experience as a peer support worker. As such, this pilot testing provides key information on the factors to consider in the implementation of this complex intervention (including recruitment and training of moderators and participant recruitment, retention, and engagement with the intervention). We will further detail and interpret these aspects of implementation using sociotechnical theory in our upcoming results report. In summary, through this study, we will gain insights into the acceptability, safety, and potential efficacy of HoryzonsCa, as well as key information that will support decision-making regarding scaling up the implementation and evaluation of this online intervention in Canada and abroad.

### Strengths and Limitations

There are several strengths to this research. First, in terms of preparing the intervention, we made adaptations to Horyzons to optimize its transferability from Australia to Canada, using a systematic approach and an eHealth adaptation framework, prior to its implementation [30,31]. The mixed methods design in this study is expected to provide an in-depth understanding of user experience and perspectives of HoryzonsCa. This mixed methods approach allows researchers to obtain a comprehensive view about the user experience and evaluate the potential impact of implementing such digital health innovations in Canadian health care settings.

Limitations of this study include a small sample size (N=20) and a single group, pre-post design. Due to this small sample size and a lack of a control group, we may not be able to detect treatment effects and impact of the intervention. Additionally, due to the short duration of follow-up (ie, 8 weeks), our findings regarding the acceptability, safety, and potential efficacy of HoryzonsCa will need to be interpreted with caution. Furthermore, our approach to exclude participants that score as moderately severe to extremely severe on suicidality (ie, due to recent suicidal ideations and behaviors, to mitigate the need for urgent intervention on a platform that is not monitored 24/7, and to reduce potential overexposure to comments that may be disruptive or distressing for other participants in the intervention) is not necessarily supported by predictive research and could even potentially exclude participants who may benefit from such an intervention [63,64]. Future research on HoryzonsCa should consider how such an online intervention platform can facilitate a recovery-oriented approach for all participants despite their score on a suicidality assessment while at the same time optimizing the safety of the online group environment. In addition, although the field of digital mental health is rapidly growing [23,61], we acknowledge that the limited evidence on the implementation of digital mental health interventions for people diagnosed with severe mental health disorders such as psychosis in Canada may limit the scope of our interpretations regarding the results. Nonetheless, the findings will help inform decision-making for scaling up the evaluation on HoryzonsCa to a larger implementation study.

